## Abstract

**Introduction:**

Lumbosacral radiculopathy/radiculitis (LR) or “sciatica” is a commonly intractable sequelae of chronic low back pain (LBP), and challenges in the treatment of LR indicate that persistent pain may have both mechanical and neuropathic origins. Mindfulness-based interventions have been demonstrated to be effective tools in mitigating self-reported pain in LBP patients. This paper describes the protocol for a randomized controlled trial (RCT) evaluating the effects of the specific mindfulness-based intervention Mindfulness-Oriented Recovery Enhancement (MORE) on LR symptoms and sequelae, including mental health and physical function.

**Methods:**

Participants recruited from the Portland, OR area are screened before completing a baseline visit that includes a series of self-report questionnaires and surface electromyography (sEMG) of the lower extremity. Upon enrollment, participants are randomly assigned to the MORE (experimental) group or treatment as usual (control) group for 8 weeks. Self-reported assessments and sEMG studies are repeated after the intervention is complete for pre/post-intervention comparisons. The outcome measures evaluate self-reported pain, physical function, quality of life, depression symptoms, trait mindfulness, and reinterpretation of pain, with surface electromyography (sEMG) findings evaluating objective physical function in patients with LR. To our knowledge, this is the first trial to date using an objective measure, sEMG, to evaluate the effects of a mindfulness-based intervention on LR symptoms.

**Hypotheses:**

We hypothesize that MORE will be effective in improving self-reported pain, physical function, quality of life, depression symptoms, mindfulness, and reinterpretation of pain scores after 8 weeks of mindfulness training as compared to treatment as usual. Additionally, we hypothesize that individuals in the MORE group with abnormal sEMG findings at baseline will have improved sEMG findings at their 8-week follow-up visit.

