## Trial design

2

This manuscript outlines the protocol for a randomized clinical trial to evaluate the efficacy of a virtually administered, 8-week MORE intervention on self-reported pain, physical function, quality of life (QoL), depression symptoms, trait mindfulness, and sEMG findings in patients with LR when compared with treatment as usual (TAU).

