### Statistical analytical plan

3.8

Participant descriptive information collected at baseline, including demographics, pain characteristics, physical function, QoL, depression, and trait mindfulness will be reported as mean (SD) or number (percent), as appropriate, for each study group. Likewise, changes from baseline to follow-up of each outcome measure will be reported as mean (SD) for each group.

*A priori* analytical modeling has been developed based on primary and secondary outcome measures and established relevant covariates. Relevant covariates (according to priority) include age, sex [7], change in treatment during study enrollment (as a binary variable), disease etiology [81,82], duration of symptoms prior to study enrollment, previous condition specific surgery [81], and baseline instrument score. To retain adequate power for linear mixed modeling, only covariates that are correlated to the outcome measure of interest (*r* ≥ .3, by Pearson or point-biserial correlation, as appropriate) will be retained. Covariates found to be significantly correlated will be added to the relevant model in a stepwise fashion in the aforementioned order.

All outcome variables aside from VAS pain (pain severity, physical function, QoL, depression symptoms, trait mindfulness, and reinterpretation of pain) will be analyzed using linear mixed modeling with maximum likelihood estimation of missing data to compare mean change between the MBI + TAU and TAU groups’. Next, we will evaluate associations between pain, physical function, QoL, depression symptoms, trait mindfulness, and reinterpretation of pain in relation to time spent practicing mindfulness amongst participants in the intervention group. The same approach will evaluate for significant differences in RMS and RMS-peak time within sEMG findings from baseline to follow-up. Finally, we will evaluate the association between changes in RMS from baseline to follow-up and change scores of the ODI, VAS, and PD-Q in participants in the intervention group.

For all models, we will complete a modified intention-to-treat analysis (mITT) including all those participants who completed the program. A per-protocol structure using only those participants in the treatment group who completed a minimum of 5 sessions synchronously will be used for sensitivity analysis as has been used previously in clinical trials and trials of MORE [41,83,84].

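### The sEMG hypothesis is an uncontrolled pre-post improvement in MORE participants selected for abnormal baseline sEMG, which conflicts with the stated comparison against TAU and is open to regression to the mean

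*Protocol article*

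**What the plan says.** The Hypotheses paragraph of the abstract makes two claims. The self-report outcomes are expected to improve "after 8 weeks of mindfulness training as compared to treatment as usual". The sEMG claim follows, and it has no such clause: "individuals in the MORE group with abnormal sEMG findings at baseline will have improved sEMG findings at their 8-week follow-up visit". It concerns one arm, one subgroup defined by its own baseline, and change over time.

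Section 2 sets a different aim. It says the trial evaluates MORE on a list of outcomes that ends with "sEMG findings in patients with LR when compared with treatment as usual (TAU".

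Section 3.8 first plans "linear mixed modeling with maximum likelihood estimation of missing data to compare mean change between the MBI + TAU and TAU groups" for a bracketed list of outcomes. The list includes physical function but does not name sEMG. The next sentence relates outcomes to practice time, "in relation to time spent practicing mindfulness amongst participants in the intervention group". Then comes the sEMG sentence: "The same approach will evaluate for significant differences in RMS and RMS-peak time within sEMG findings from baseline to follow-up". It names no group contrast, and it restricts the analysis neither to MORE nor to abnormal baselines.

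sEMG is collected in both arms. Section 3.2 places it at the baseline visit, before randomisation, and repeats it at follow-up without restriction by arm.

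**The concern.** When people are selected because a noisy measurement was abnormal, the next measurement is on average closer to normal whether or not anything was done to them. Natural recovery and familiarity with the test can move it in the same direction. A pre-post improvement in abnormal-at-baseline MORE participants cannot separate these from an effect of MORE. The same selection applied to TAU participants carries the same artefact, so a contrast between arms removes it.

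This matters because sEMG is the trial's objective measure, and the article presents its use with a mindfulness intervention in this condition as a first. As worded, the hypothesis could be declared met by a result that is not evidence that MORE improved muscle function, while section 2 leads the reader to expect a randomised comparison.

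**Working it through.** **The plan's own figure.** The article gives no sEMG calculation. Its only sample size (section 3.7) is for the Oswestry Disability Index. A two-sample t-test with d = 0.83, two-sided alpha 0.05 and 80% power needs 23.8, so 24 per group or 48 in all; 48 / 0.80 = 60. This reproduces. It is used here only to say how many MORE completers to expect: 24.

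**Time between the two sEMG recordings.** Up to 16 weeks from baseline to randomisation (section 3.2), 8 weeks of intervention, and up to 6 weeks to the follow-up visit (section 3.3): 16 + 8 + 6 = 30 weeks.

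**Assumptions, because the article gives neither figure.** Baseline to follow-up correlation r = 0.6 to 0.9. Share of participants abnormal q = 30% to 50%. Abnormal is modelled as the worst tail of a normally distributed measure, with equal means and SDs at both visits and no true change.

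**Expected apparent improvement**, in baseline SDs: (1 − r) × φ(z_q) / q, where z_q is the normal quantile at q and φ the normal density.

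- q = 0.30: φ(−0.524) / 0.30 = 0.348 / 0.30 = 1.159
- q = 0.50: φ(0) / 0.50 = 0.399 / 0.50 = 0.798

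**Number tested.** 24 × 0.30 ≈ 7 and 24 × 0.50 = 12 MORE completers.

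**Rejection rate with no true effect.** Simulated (100,000 trials per row), paired t-test at two-sided 5% in the selected MORE completers, beside a two-sample test of change between equally selected MORE and TAU participants:

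| q | n in MORE | r | Expected shift (SD) | Paired test rejects | MORE vs TAU rejects |
|---|---|---|---|---|---|
| 0.30 | 7 | 0.6 | 0.46 | 24% | 5% |
| 0.30 | 7 | 0.8 | 0.23 | 13% | 5% |
| 0.30 | 7 | 0.9 | 0.12 | 9% | 5% |
| 0.50 | 12 | 0.6 | 0.32 | 23% | 5% |
| 0.50 | 12 | 0.8 | 0.16 | 13% | 5% |
| 0.50 | 12 | 0.9 | 0.08 | 9% | 5% |

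Nearly all paired-test rejections are in the favourable direction. These rows cover regression to the mean only; natural change over the 30 weeks is not included.

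**Reading section 3.8.** The phrase about using the same approach has two possible antecedents. One is the between-group mixed model, the only modelling method named in that paragraph. The other is the practice-time analysis within the intervention group, which is the sentence immediately before. The text does not decide between them.

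**The case against.** The strongest reply is that the analysis plan may already be comparative. Section 3.6 describes sEMG as an objective measure of physical function and says RMS and RMS peak time will be used to analyse physical function. Physical function is in the list for the MORE-versus-TAU mixed model, and section 2 announces a comparison with TAU. A between-arm comparison of change is also a comparison from baseline to follow-up. This stands as a plausible reading. A reader might infer that the plan contains no between-arm sEMG analysis; the article does not establish that. What the reply does not do is change the hypothesis, which a one-arm result would satisfy, or explain why sEMG has a sentence of its own with no arms in it.

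Second, the abnormal-baseline restriction appears only in the hypothesis, and no paired t-test is specified anywhere. That is correct: the figures above are conditional on testing the hypothesis as worded. Without selection on baseline sEMG, the calculated artefact does not arise, although natural change would remain.

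Third, the size depends on repeatability and on how abnormality is judged. Section 1.1 points to comparing the symptomatic with the asymptomatic side, for which a single-tail cutoff may be a poor model. This also stands.

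Fourth, the Discussion treats the sensitivity of sEMG to change as partly an open question about the instrument, and the sample size rests on another outcome. This lowers the priority but does not remove the conflict.

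A reader might also object to relating RMS change to "change scores of the ODI, VAS, and PD-Q in participants in the intervention group" only. Using one arm costs precision, but it is a legitimate exploratory question and not an error.

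**Conclusion.** The point holds for the hypothesis and for its conflict with section 2. The sEMG hypothesis is a pre-post claim in one arm, selected on the outcome's own baseline, while the trial design promises a comparison with TAU and collects the data for one. Section 3.8 leaves open which of the two will be run.

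If tested as worded, the expected spurious improvement is about 0.08 to 0.46 SD, and the error rate is about 9% to 24% against a nominal 5%. Both ranges rest on an assumed correlation of 0.6 to 0.9, an assumed 30% to 50% abnormal, a normal-tail definition of abnormal, and 7 to 12 selected MORE completers. The number could be smaller, because section 3.3 lets participants complete follow-up questionnaires virtually.

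It would be too strong to say that a false sEMG finding is certain. The direction of the bias is expected whenever the correlation is below 1, but under these assumptions most null trials (about 76% to 91%) would still not reach significance. Nothing here touches the Oswestry comparison on which the trial is sized. The wording should be corrected before sEMG results are seen.

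**What to change.** 1. Restate the sEMG hypothesis as a difference between MORE and TAU, in line with section 2.
2. In section 3.8, replace the reference to the same approach with an explicit statement: RMS and RMS peak time are compared between arms, with baseline sEMG as covariate, in all randomised participants with sEMG data.
3. If an abnormal-baseline subgroup is reported, define it by one rule applied to baseline data in both arms, and compare MORE with TAU within it. A change within MORE alone should be presented as descriptive.

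The cost is wording only; sEMG is already planned in both arms at both visits. The one downside is that the sEMG result may look less favourable than a pre-post test would.

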## Introduction

1

### Background and rationale

1.1

Low back pain (LBP) is a ubiquitous musculoskeletal complaint that often presents as a chronic, intractable condition with an estimated lifetime prevalence of 85.5% [1,2] and global point prevalence of 8.2% [3]. Lumbosacral radiculopathy/radiculitis (LR), also known as “sciatica”, is a secondary neuropathic condition to LBP, affecting approximately 37% of this population [4]. LR is most frequently caused by compression of the L4-S1 nerve roots, subsequently causing pain, sensory loss, motor/reflex abnormalities, and weakness [5,6].

Diagnosis of LR is completed using electrodiagnostic studies, magnetic resonance imaging, and/or physical examination. Surface electromyography (sEMG), a type of electrodiagnostic study, has been found to be an effective tool in assessing LR based on its ability to differentiate between compressive and non-compressive radiculopathies [4,7] as well as its strong diagnostic accuracy (93.6%) for differentiating between the most common distal spinal disc herniations, L5 and S1 [8,9]. sEMG assesses muscle tone and function on the lower legs while walking. LR is characterized by pain and dysfunction in the lower extremity; thus, evaluating muscle function between symptomatic and asymptomatic sides provides clear objective data regarding physical function. Additionally, sEMG has been used to quantify the severity of impairment in motor function and thus may help elucidate relationships between objective functional data and self-reported pain scores.

In addition to being pervasive, treatment for LR patients is financially burdensome. The U.S. estimated annual costs of spinal fusions in 2015 was $10 billion, and indirect costs of general chronic pain has been estimated to total $100 billion annually [10,11]. These indirect costs comprise the most financially burdensome element of neuropathic pain management [12]. Mental health burdens associated with LBP are also significant [1,6], with studies reporting rates of depression up to 72% in samples of chronic pain patients [13]—suggesting that treatment of mood symptoms in chronic pain patients may decrease both health care costs and pain-related dysfunction [14,15]. Prescription pain management, including opioid medications, is common in this population due to otherwise ineffective and expensive treatment options, resulting in 19% of these patients eventually becoming long-term users of opiates [16].An estimated 29% of chronic pain patients will misuse and 11% will abuse opiates, underscoring the need for alternative treatments for LBP patients that do not have associated risk for dependence, abuse, and addiction [17].

The burdens associated with LR warrant a more cost-effective and safe pain management strategy. Research has shown mindfulness-based interventions (MBIs) are more cost-effective than usual care [18] and effective in limiting self-reported pain in patients with chronic LBP, neuropathic conditions, and depression [[19], [20], [21], [22], [23], [24], [25], [26], [27], [28]]. Potential mechanisms for the relationship between mindfulness practice and self-reported pain include decreases in reactivity of immune and supraspinal pathways within and between the amygdala [29], pro-inflammatory cytokines [30], thalamus, and periaqueductal gray matter [31]. Though MBIs have been effective in other pain management contexts, including generalized LBP, sufficient demonstrative evidence of the efficacy of MBIs for pain management in LR specifically is lacking.

Mindfulness-Oriented Recovery Enhancement (MORE) was developed for the treatment of addiction, stress, and pain using cognitive-behavioral therapy and positive psychology to help disrupt attentional bias towards pain in chronic pain conditions [[32], [33], [34], [35], [36], [37],^39^]. It differs from other MBIs such as mindfulness-based stress reduction in its focus on the development of reappraisal and savoring practices. These appear throughout the program as key tenets of the pain restructuring process and are able to achieve reductions in pain perception by shifting participants’ attention from affective processing to sensory processing and reducing experiences of anhedonia by regulating negative emotional states [38]. [name], the developer of MORE, proposes a model “leveraging [three] natural rewards:” savoring natural rewards, noticing and generating pleasant internal states, and cultivating meaning and self-transcendence [39]. When MORE was evaluated for its 9-month impact on chronic pain and opioid use against a supportive psychotherapy program, 45% of MORE participants ceased misusing opioids after 9 months, and 50% of MORE participants saw a minimally clinically important change in pain severity. This is compared to 24.4% in opioid misuse cessation and 29.3% for pain severity changes in the supportive psychotherapy group [40]. Although various MBIs have been investigated for their effects on LBP [[19], [20], [21], [22], [23], [24], [25],^36^,^41^], few studies have specifically evaluated the effectiveness of MBIs for LR symptoms, and none have attempted to deliver MORE virtually in this subpopulation. To our knowledge, this is also the first trial to date using an objective measure, sEMG, to evaluate the effects of a MBI on LR symptoms.

## Trial design

2

This manuscript outlines the protocol for a randomized clinical trial to evaluate the efficacy of a virtually administered, 8-week MORE intervention on self-reported pain, physical function, quality of life (QoL), depression symptoms, trait mindfulness, and sEMG findings in patients with LR when compared with treatment as usual (TAU).

## Methods

3

### Study setting

3.1

IRB approval was received for this protocol at the National University of Natural Medicine (NUNM), and study recruitment began in February 2021 (IRB #: KP112720; clinicaltrials.gov #: NCT04818606). Recruitment is conducted through flyers at the NUNM academic and clinic buildings as well as clinical partnerships with the Oregon Health & Science University Spine Center and Comprehensive Pain Center, Northwest Integrative Medicine, and other local primary care clinics. Additionally, flyers are posted in local grocery stores and community newsletters. Clinical partnerships consist of a 2-part recruitment strategy: 1) query of patients via clinic electronic medical records using ICD-10 code, age, and being English-speaking as search criteria; or 2) direct referral from physicians to our study e-mail and phone number. Once contact information for eligible patients is received via queries with partner clinics, recruitment letters are sent. Two weeks later, study staff reach out via phone to conduct screenings and schedule baseline visits with potential participants.

Participants undergo a telephone screening and interested participants who meet all eligibility criteria are invited to schedule a baseline visit at NUNM's Helfgott Research Institute building in Portland, OR. Participants without a previous LR diagnosis (Table 1, inclusion criterion 1b) may be eligible to schedule a baseline study visit if meeting a minimum pain score of 15 on the modified painDETECT Questionnaire (PD-Q). Eligibility criteria are summarized in Table 1.

**Table 1 tbl1:** Eligibility criteria.

Inclusion Criteria	Exclusion Criteria
1a) Presence of lumbosacral radiculopathy/radiculitis symptoms that extend below the knee secondary to low back pain for greater than 6 weeks with a painDETECT score greater than 15 OR	1) Have received epidural steroid injection in the prior 3 months
1b) Diagnosis of lumbosacral radiculopathy/radiculitis secondary to low back pain that extends below the knee, with symptoms present for greater than 6 weeks with the following ICD-10 codes: M54.16, M54.17, M51.16, M51.17, M47.26, M47.27, M54.40, M54.41, M54.42, M99.53, M99.54, S34.21, S34.22, G54.4, and G55	2) Inability to complete 20 unassisted gait cycles
2) At least 18 years of age and not older than 65 at the time of study enrollment.	3) Have received a surgical intervention for low back pain or lumbosacral radiculopathy/radiculitis within the previous 6 months
3) Ability to read and understand English	4) Current active mindfulness meditation practice: 1 time/week or more and/or formal training in mindfulness/meditation practice
4) Willingness to be randomized to either an experimental or a control group	5) Concurrent diagnosis of cancer
5) Willingness to refrain from unnecessary or self-directed pain management/treatment plan changes during study enrollment and to report necessary changes made	6) Allergy or intolerance to adhesive
6) Daily access to the internet via cell phone, tablet, or computer	7) Current unmanaged or uncontrolled mental illness known to cause psychosis: schizophrenia and schizotypal disorders, bipolar I disorder with psychosis, major depressive disorder with psychosis

### Study design

3.2

Baseline visits conducted at Helfgott Research Institute include confirmation of eligibility criteria, informed consent, study questionnaires, and sEMG collection for 20 gait cycles. Follow-up visits include all steps except repeated informed consent. All participants receive an email containing the informed consent document after baseline visit. Within 16 weeks of baseline visit completion, participants are randomized to either an 8-week MBI and treatment as usual (MBI + TAU) or TAU-only group to be completed in parallel cohorts. Both groups are asked to refrain from changes to their current treatment plan whenever reasonable (i.e., to avoid self-directed changes in treatment such as starting a new supplement) and to report any medically necessary (i.e., physician-recommended or -implemented) changes made during study enrollment. All study participants receive a copy of a pain education handout, “Understanding Pain,” at the time of intervention initiation as an effort to reduce the disparity upon health education [42]. This handout is provided publicly by the Oregon Pain Management Commission. Participants in both groups are asked to report daily pain levels using a Visual Analog Scale (VAS) administered via text message or email as preferred per participant.

Treatment as usual was chosen as the control condition for this experiment, as experts recommend using TAU control groups in studies of MBIs based on evidence from other RCTs conducted in this realm [43]. MORE has not been studied in the context of LR, and no gold standard has been identified as an active control for MORE in this subpopulation; therefore, TAU was deemed as appropriate for this study design. The control group undergoes TAU over 8 weeks of parallel group comparison and starts their 8-week enrollment period on the same day as the experimental group. Participants assigned to the TAU control group are offered to join a MORE program be delivered after the data collection period of the trial has ended. Our study team offered this option as we anticipate a benefit from MORE in the management of lumbosacral radiculopathy. A study flowchart can be seen in Fig. 1.

